## Abstract

The main aim of this study is to systematically record Cerebrolysin treatment modalities and concomitant medication, according to local standards, in patients with moderate to severe neurological deficits after acute ischemic stroke and to assess the impact of these parameters on therapy outcome during early rehabilitation (day 21) and on day 90. An open observational treatment design based on the principles of high-quality comparative effectiveness research (HQCER) has been chosen to capture the therapies as applied in real-world clinical practice. HQCER opens a new horizon for strengthening the validity of the results from observational trials, thereby enhancing the associated level of evidence. Rigorous pre-specification of analytical procedures and tight risk-based centralized monitoring were additional measures to improve the impact of the observational approach. The value for real-world studies has become obvious, and such studies based on comparative effectiveness designs supplement the classical study designs by enabling the inclusion of larger proband numbers and more statistical reliability for practical use.

## Introduction

### Background information

#### Methodological Considerations

Observational studies are best used to evaluate the real-world applicability of evidence derived from randomized trials [1]. However, in terms of rating quality of evidence, observational trials usually begin as low-quality evidence, limiting the validity and generalizability of the observational results GRADE Guidelines *Rating the quality of evidence* [2, 3]. Recent suggestions for high-quality comparative effectiveness (CE) research GRACE principles for *Good Research for Comparative Effectiveness OBSERVED* [4, 5], in combination with rigorous risk-based centralized monitoring approaches (see EMA [6], FDA [7] risk-based guidance) open new perspectives for enhancing the level of evidence of observational trials.

Thus, in agreement with current recommendations, the present design of an observational registry study has chosen a high-quality comparative effectiveness approach.

#### Treatment

Cerebrolysin is a neuropeptide preparation with marketing authorization to treat cerebrovascular disorders and neurodegenerative diseases for many years worldwide. Since its first approval, stroke therapy has developed, and new treatment concepts have been implemented. In addition, over time, Cerebrolysin treatment in stroke has evolved with different time windows, dosages, and duration of therapy, often being given pragmatically by physicians. Therefore, the main aim of this study is to capture these variables of Cerebrolysin treatment and its comedication in patients with moderate to severe neurological deficits after acute ischemic stroke to guide further research.

C-REGS 2 is an international, non-interventional, prospective registry study to observe clinical practices of routine use of Cerebrolysin in patients with moderate to severe neurological deficits after acute ischemic stroke in a controlled and open-label manner. According to local treatment standards, all patients receive acute stroke care, which is not amended or influenced by the study. The outcome of Cerebrolysin-treated patients is compared with control group patients, who do not receive Cerebrolysin to evaluate the safety and effectiveness of Cerebrolysin in routine practice.

## Material and Methods

### Study Objectives

The objective of this registry study was to observe clinical practices, safety, and effectiveness of routine use of Cerebrolysin in the treatment of patients with moderate to severe neurological deficits after acute ischemic stroke, based on principles of high-quality comparative effectiveness research (HQCER).

### Study Design

Non-interventional, controlled, open-label, prospective, multicentre, high-quality comparative effectiveness observational registry study.

### Patient population

Criteria for observed patient population:

•Signed Informed Consent;•Clinical diagnosis of acute ischemic stroke, confirmed by imaging;•Moderate to severe neurological deficits (observation window: NIHSS 8-15);•No prior stroke;•No prior disability;•Patient’s independence before stroke onset (premorbid mRS of 0 or 1);•Reasonable expectation of successful follow-up (max. 100 days).

### Investigational Product

Cerebrolysin has marketing authorization in the countries participating in C-REGS 2. C-REGS 2 is an observational study. Thus, the treatment of patients follows standard hospital practices and is separated from the decision to include a patient in the study.

#### Name and Description of the Investigational Product

Cerebrolysin is a neuropeptide preparation produced by a standardized enzymatic breakdown of purified, lipid-free porcine brain proteins. It consists of low molecular weight neuropeptides (<10 kDa) and free amino acids. Cerebrolysin has been used to treat cerebrovascular and neurodegenerative diseases, including stroke, dementia, and traumatic brain injury, for many years.

#### Dosage, Formulations, and Administration

Dosage, frequency, duration, and mode of administration of Cerebrolysin follow the local hospital practice following the terms of the local marketing authorization and are not amended or influenced by the study. Prescribed Cerebrolysin will be used as a solution for injection/concentrate for solution for infusion.

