The advantage of the chosen multilevel case-mix standardization compared to other, model-based approaches such as regression models is that any assumption about the nature of risk-outcome relation is avoided, allowing true *like-to-like* comparisons. Furthermore, some potential drawbacks of other procedures, as the model-based propensity score matching with its risk of bias due to incomplete matching [53], are reduced.

According to the Principles for Good Research on Comparative Effectiveness (GRACE) recommendations, the study size intended for the observational trial “should be described including a description of how that size was determined, what specific assumptions are being made, and how well these assumptions are supported”. As this is an observational study, the relations among effect size, sample size, and power estimates are indicative only. However, some justification is needed to support the planning of the number of centers and the duration of the enrolment period. Thus, within the framework of the chosen study design, we performed a fully elaborated sample size calculation based on the pre-specification of the analytical techniques.

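### Controls are not required to have been eligible for Cerebrolysin, so patients who could not have received it can enter only as controls, and the planned stratification cannot correct for that

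*Protocol article*

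**What the plan says.** Five places in the article bear on this point.

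- **Treatment.** The comparison group consists of "control group patients, who do not receive Cerebrolysin". No reason for non-use is asked for, and it is not required that the drug was an option.
- **Patient population.** One list serves both groups: consent, imaging-confirmed ischemic stroke, NIHSS 8-15, no earlier stroke, no earlier disability, premorbid mRS 0 or 1, and a reasonable prospect of follow-up. Nothing in it concerns suitability for Cerebrolysin.
- **Investigational Product.** "Cerebrolysin has marketing authorization in the countries participating in C-REGS 2", and treatment "is separated from the decision to include a patient in the study". No country is control-only for want of a licence, but enrolment does not depend on whether a patient could be treated.
- **Dosage, Formulations, and Administration.** The dose of the drug, how often and how long it is given, and its route "follow the local hospital practice following the terms of the local marketing authorization". The subject of the sentence is how the drug is given, not who may receive it.
- **Case-Mix Standardization.** NIHSS, small vessel disease, diabetes and age are handled by stratification. Earlier stroke and earlier disability are handled by the restricted cohort. No variable describes eligibility for the drug.

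The Discussion nevertheless presents the scheme as "allowing true *like-to-like* comparisons".

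**The concern.** A stratified comparison of treated and untreated patients needs every patient in a stratum to have had some chance of either exposure (positivity, or overlap). General Principles and the Discussion both concede that choosing treatment on clinical features invites confounding, and the case-mix scheme is the answer to that. The scheme can balance only the variables it contains, and only where both groups are represented. A patient whom the local authorization rules out has no chance of treatment. Under the stated criteria such a patient is still enrolled, counts as a control, and is pooled with controls who could have been treated and who share the same NIHSS score, age group, diabetes status and small vessel disease status.

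If these patients differ in prognosis from the others in their stratum, the day-90 mRS comparison shifts for a reason unrelated to the drug. The same holds for mortality, serious adverse events and adverse events, which use the same adjustment. The sensitivity analyses in the intention-to-include population do not help, because nothing stated removes these patients there either.

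**Working it through.** **Plan's own figure.** The article gives no figure for this point, so there is nothing to reproduce. It supplies only the scale: a difference to be detected of MW = 0.55, which is 0.05 above the null, a planned total of about 2000, a maximum imbalance of 1:2, and stage I at about 30%, or 0.3 × 2000 = 600 patients.

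**Assumed inputs (not in the article).**
- f, the share of controls who could not have received Cerebrolysin: 1% to 10%.
- q, the MW for treated patients against those controls when the drug has no effect: 0.5 (same prognosis) to 0.7 (clearly worse prognosis).

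**Formula for the shift.** With no true effect, treated patients against the other controls have MW 0.5. The observed value is the mixture

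MW = 0.5(1 − f) + f·q = 0.5 + f(q − 0.5).

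**Formula for the rejection rate.** The Noether standard error is 1/√(12·N·c(1 − c)) with c = 1/3.
- N = 2000: 12 × 2000 × 2/9 = 5333, so SE = 0.0137.
- N = 600: 12 × 600 × 2/9 = 1600, so SE = 0.025.

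The rates below are for a single-stage two-sided test at 0.05 without stratification, so they are indicative only.

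| f | q | Observed MW | Share of the 0.05 design excess | Rejection under the null, N = 2000 | N = 600 |
|---|---|---|---|---|---|
| any | 0.5 | 0.500 | 0% | 5.0% | 5.0% |
| 1% | 0.6 | 0.501 | 2% | 5.1% | 5.0% |
| 5% | 0.6 | 0.505 | 10% | 6.5% | 5.5% |
| 5% | 0.7 | 0.510 | 20% | 11.3% | 6.9% |
| 10% | 0.7 | 0.520 | 40% | 30.9% | 12.6% |

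Worked line: f = 0.10 and q = 0.7 give 0.5 + 0.10 × 0.2 = 0.520. The excess of 0.020 is 0.020/0.05 = 40% of the design excess and 0.020/0.0137 = 1.46 standard errors at N = 2000.

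**Direction.** The sign depends on q. If patients ruled out for the drug had the better prognosis, q would lie below 0.5 and the shift would go against Cerebrolysin. For example, q = 0.3 and f = 0.10 give 0.5 − 0.10 × 0.2 = 0.480.

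**With a common criterion.** If both groups must be eligible under the same authorization terms, f = 0 and this source contributes nothing.

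**The case against.** The strongest objection is that the authorization sentence does not select patients. It ties dosage, frequency, duration and mode to local practice and the local label. A reader might infer that treated patients must satisfy the label while controls need not. The article does not say that. It is a reasonable inference that use within an authorization respects its limits on who is treated, but it remains an inference.

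The article also names no contraindication and does not say how common one would be in this cohort. A reader might conclude that such patients do worse and so make Cerebrolysin look more effective and safer than it is. No statement in the article supports that direction. Nor does anything support a large share: 20% of controls with q of 0.6 to 0.7 would give 0.520 to 0.540, but no figure points to 20%. The cohort is already restricted on stroke severity and premorbid state, and the relevant q is the difference left within strata, which may be small.

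The article also condenses a full protocol, an operational manual and an SAP that are not shown, and one of them may contain such a criterion. The general confounding problem is acknowledged in the text.

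All of this limits the size and certainty of the point. It does not remove the gap. The article presents its list as the criteria for the observed population and describes the restricted cohort as covering two conditions only. Acknowledging confounding in general also does not answer a lack of overlap, which adjustment for the listed variables cannot repair.

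**Conclusion.** The point holds in a limited form. The eligibility list, the control definition and the case-mix scheme, as stated, do not make controls eligible for Cerebrolysin on the same terms as treated patients. If treatment respects the authorization's limits, patients outside them can be present only among controls, and the planned stratification cannot find them a treated counterpart. The like-to-like claim in the Discussion is therefore stronger than the design supports.

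The comparisons may be biased; the article does not show that they are. Under the assumed ranges for f and q, and ignoring stratification, the spurious MW is 0.500 to 0.520, or 0% to 40% of the distance from the null to the design effect. The corresponding null rejection rate is 5% to about 31% at N = 2000, and 5% to about 13% at 600. The effect may be nil, and its direction is unknown. This is a cheap improvement to the design, not a demonstrated error in its results.

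**What to change.** Extend the restricted cohort, which the plan already uses, by one criterion for both groups: no contraindication to Cerebrolysin under the local marketing authorization at inclusion. Record it as a yes/no item in the eCRF. The criterion depends on the patient's condition and not on the treatment given, so inclusion stays separate from the treatment decision and nobody's care changes.

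For patients already enrolled, keep the pre-specified Target Population for the primary analysis. Where the data exist, add a sensitivity analysis that excludes controls who could not have been treated. Redefining the main analysis set afterwards would undo a pre-specification and would need data that the article does not show were collected.

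The cost is one eligibility line, one eCRF item and a few fewer controls. Because authorizations are local, what the item excludes may vary somewhat between countries.

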### Concomitant Therapy

Concomitant medication is not restricted or influenced by the study and is documented in the eCRF.

### Assessment of Effectiveness

No additional diagnostic, therapeutic, or monitoring procedures other than those used according to local practice will be applied to the patients included in the study. Tests selected to assess effectiveness have been chosen per the recommendations of various stroke guidelines:

The *Modified Rankin Scale* [8] (mRS) measures the level of disability after stroke and has been widely used for many years in clinical practice to measure global functional outcomes.

The mRS assessment is performed using the Rankin Focused Assessment (RFA) [9, 10] to provide clear operationalization and ensure consistent score determination across raters.

The *National Institutes of Health Stroke Scale* (NIHSS) is a systematic assessment tool that provides a quantitative measure of stroke-related neurological deficits. It is described as the standard for the assessment in acute stroke in the “Guidelines for the early management of patients with acute ischemic stroke” by the American Heart Association/American Stroke Association, the ESO Guidelines for “Management of Ischemic Stroke and Transient ischemic Attack” and in the Austrian Neurology Society (ÖGN-ÖGSF) guideline (Chapter 12) [10, 11].

The NIHSS reflects neurological impairment, the clinical domain in which early effects of acute stroke therapies are likely to be most marked. Recent research showed that the NIHSS is most sensitive for early points in time [12]. Furthermore, it is less influenced by extraneous factors, improving sensitivity to acute treatment effects. A trained observer rates the patient’s ability to answer questions and perform activities. Ratings for each item are scored with 3 to 5 grades with 0 as normal, and there is an allowance for untestable items. The single patient assessment requires less than 10 minutes.

The assessment of cognitive deficits following stroke is recommended by several guidelines (ESO Guidelines, Austrian Neurology Society [13] and the DEGAM Stroke Guideline nr. 8). The DEGAM guideline mentions the Mini-Mental State Examination (MMSE) for assessment. However, compared to the MMSE, the *Montreal Cognitive Assessment* (MoCA) was shown to be more sensitive for the detection of cognitive impairment after acute stroke [14] and is recommended by the “National clinical guideline for Stroke” [15]. The MoCA is a screening tool for mild cognitive dysfunction, which takes approximately 10 minutes [16]. The possible maximum score is 30 points, and 26 or above is considered normal.

The *Informant Questionnaire on Cognitive Decline in the Elderly* (IQCODE) is described as a valuable tool to assess premorbid cognitive dementia [17], which has been widely adopted in clinical practice [18]. The IQCODE is a prerequisite for the MoCA assessment to identify patients with cognitive dysfunction before a stroke. It is filled out by a person who has known the patient for ten or more years.

#### Mandatory Training of Scales

For the NIHSS, the mRS, and the MoCA, mandatory training has to be performed by all personnel using the scales. The rating has to be performed by site personnel that is independent of treatment administration.

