#### Effectiveness Evaluation

Ordinal analysis of the modified Rankin scale (mRS) three months after stroke onset is chosen as a clinically relevant primary endpoint for final treatment effects. The leading secondary endpoint is the NIHSS score on days 21 and 90.

The technical operationalizations for the first-line analysis of the primary and secondary effectiveness measures, based on observed cases (OC) and target population (see section Analysis Sets), are as follows:

•Primary outcome measures (effectiveness evaluation)•Secondary outcome measures (effectiveness evaluation)

1.Ordinal modified Rankin Scale (mRS) at 3 months after stroke onset, absolute scores, Mann-Whitney Effect Size (MW) [20–25], OC, Target Population;2.Ordinal NIH Stroke Scale (NIHSS) at 21 days and 3 months after stroke onset, absolute scores, Mann-Whitney Effect Size (MW), OC, Target Population;3.Ordinal modified Rankin Scale (mRS) at 21 days after stroke onset, absolute scores, Mann-Whitney Effect Size (MW), OC, Target Population;4.Proportion of patients with excellent recovery (mRS score 0–1) at three months after stroke onset, Odds Ratio, OC, Target Population;5.Proportion of patients with functional independence (mRS score 0–2) at three months after stroke onset, Odds Ratio, OC, Target Population;6.Ordinal MoCA at 3 months after stroke, Mann-Whitney Effect Size (MW), OC, Target Population.

According to the ICH Guideline E9 (ICH Topic E9, Statistical Principles for Clinical Trials, Step 4, Consensus guideline, 5 February 1998, CPMP/ICH/363/96) the results will be given as P-values as well as effect size measures with their associated confidence intervals (outcome no. 1, 2, 3, 6: Mann-Whitney effect size; outcome no. 4 and 5: odds ratio, supplemented by Mann-Whitney effect size for inter-outcome comparisons [25]), so that the direction and quantity of the treatment effects are determined with their precision.

The Mann-Whitney effect size [20–25] is the most valuable effect size measure for nonparametric approaches based on the well-known Wilcoxon framework because it is valid in data situations where the Hodges-Lehmann shift parameter is no longer appropriate. Furthermore, the Mann-Whitney effect size is appropriate for continuous, ordinal, and binary data at the same time and represents an ideal effect size measure. Incidentally, the 25^th^ Anniversary of the journal Statistics in Medicine dedicated a whole issue to papers about the Mann-Whitney statistic [20].

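### Outcome raters must not administer the treatment but need not be unaware of it, so in this open-label comparison the primary mRS is open to exposure-dependent rating bias that masked rating would reduce

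*Protocol article*

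**What the plan says.** Under Mandatory Training of Scales, for the NIHSS, mRS and MoCA, "mandatory training has to be performed by all personnel using the scales", and "The rating has to be performed by site personnel that is independent of treatment administration". No other sentence in the article says who rates or what the rater may know.

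The setting in which the rule operates:

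- Study Design: "Non-interventional, controlled, open-label, prospective, multicentre".
- Treatment: "The outcome of Cerebrolysin-treated patients is compared with control group patients, who do not receive Cerebrolysin". The comparator is absence of the drug, with no dummy infusion to conceal it.
- Effectiveness Evaluation: "Ordinal analysis of the modified Rankin scale (mRS) three months after stroke onset is chosen as a clinically relevant primary endpoint". The other five ordered outcomes are NIHSS, mRS at day 21, two mRS dichotomies and MoCA. All six come from the three rated scales.
- Assessment of Effectiveness: "The mRS assessment is performed using the Rankin Focused Assessment (RFA"), the stated purpose being uniform scoring between raters. The same section says "No additional diagnostic, therapeutic, or monitoring procedures other than those used according to local practice will be applied" to the patients.

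**The concern.** Taking no part in giving a drug is different from not knowing that it was given. Site staff can learn exposure from the chart, from colleagues or from the patient. A rater who has done so still complies with the rule as written.

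The three scales all need judgement. If that judgement leans one way when the rater knows the exposure, the error differs between the groups and enters the Mann-Whitney estimate directly. The case-mix standardization compares patients within the same baseline NIHSS score, age band, diabetes status and small vessel disease status. Rating error arises after baseline and inside every stratum, so pooling over strata carries it through unchanged. The study is sized for a small effect (MW=0.55), so even a modest lean is large relative to the target. Because the secondary outcomes are rated too, the same lean could pass down the fixed testing sequence.

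**Working it through.** **Reading check.** The article names three groups of safeguards that might cover this.

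1. Confounder control (General Principles, Case-Mix Standardization) acts on baseline variables and on eligibility, not on how the outcome is scored.
2. The Rankin Focused Assessment and scale training make scoring more uniform and leave less room for judgement. Neither hides exposure.
3. Centralized statistical monitoring with targeted on-site visits concerns data quality and study conduct. The article does not describe it as addressing the rater's knowledge of exposure.

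**Illustration of size.** The plan has no figure of its own on this point to reproduce.

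Inputs from the article: target MW 0.55; total 1745 before the dropout allowance; 1:2 allocation; stage I 30% of the total; stop with success at p1 ≤ 0.0299; stop for futility at p1 ≥ 0.3; stage II success at p1·p2 ≤ 0.0087. These levels are coherent: 0.0299 + 0.0087·ln(0.3/0.0299) = 0.04996.

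Inputs assumed, not in the article: day-90 mRS 0 to 6 distributed 10/17/15/18/20/8/12% in both groups (no true effect), and a share f of treated patients with mRS 1–5 scored one grade too well.

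*Step 1, MW.* Moving one patient from grade k to k−1 raises that patient's chance of being better off than a control patient by half of (p(k−1) + p(k)). Hence

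MW = 0.5 + f · Σ p(k)·[p(k−1)+p(k)]/2, for k = 1 to 5.

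The terms are 0.02295 + 0.02400 + 0.02970 + 0.03800 + 0.01120 = 0.12585, so MW = 0.5 + 0.12585·f.

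*Step 2, standard error.* SE(n) = 1/√(12·c·(1−c)·n) with c = 1/3. At n = 1745 this is 0.01466. Stage I (30%) gives 0.01466/√0.3 = 0.02676 and stage II (70%) gives 0.01466/√0.7 = 0.01752.

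*Step 3, rejection rate.* The stage z-statistics have means (MW−0.5)/0.02676 and (MW−0.5)/0.01752. The probability of rejection is P(p1 ≤ 0.0299) plus the integral over 0.0299 < p1 < 0.3 of P(p2 ≤ 0.0087/p1), with two-sided p-values, by numerical integration.

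| f | MW | Share of the 0.05 target | Mean z, stage I / II | Rejection rate |
|---|---|---|---|---|
| 0 | 0.5000 | 0% | 0 / 0 | 5.0% |
| 5% | 0.5063 | 13% | 0.24 / 0.36 | 6.0% |
| 10% | 0.5126 | 25% | 0.47 / 0.72 | 9.4% |
| 20% | 0.5252 | 50% | 0.94 / 1.44 | 24.9% |

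At f = 40%, MW = 0.5 + 0.12585·0.40 = 0.5503, which is the whole target effect.

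**Sensitivity.** Correcting the variance for ties (factor 0.975) gives 6.1%, 9.5% and 25.5%. With 1:1 allocation and no tie correction the rates are about 6%, 10% and 28%. Three other assumed distributions were tried: uniform, 8/15/15/17/20/12/13% and 15/22/20/15/13/6/9%. With the tie correction, f = 10% gives MW 0.510–0.513 and rejection of about 8–10%; f = 20% gives 0.520–0.527 and about 18–28%. The calculation ignores the stratified pooling.

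**The case against.** The strongest reply is that this is a condensed article of a declared open-label, non-interventional registry. It states a real safeguard, namely trained raters kept apart from treatment administration, and nowhere says they know the exposure. An operational manual exists and is not shown; rater procedure could sit there. No stated number is wrong and no two passages conflict. The structured interview, training and monitoring also make a misrating rate as high as 20% less likely.

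Much of this stands as a limit on the claim. A reader might infer that the raters are in fact unmasked; the article is silent on that and does not support it. A reader might also take the 25% as the trial's false-positive rate, or assume that the error touches only treated patients and always favours the drug. The documents give no misrating rate, no direction and no group, and the mildest scenario moves the rate only from 5% to 6%.

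What does not stand is the argument from silence on the rule itself. The article does not leave the rater requirement to another document. It states one as an obligation and stops before the property that protects the endpoint. The manual is mentioned only for the definitions of predictor variables. Open-label treatment does not preclude masked rating, and keeping the rater unaware adds no diagnostic, therapeutic or monitoring procedure.

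**Conclusion.** The point holds as a weakness in a stated rule: raters must be independent of treatment administration, but need not be unaware of exposure. The primary mRS and the rated secondary outcomes are therefore open to exposure-dependent rating bias that baseline stratification cannot remove and that the structured interview and training only narrow.

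On the assumed distribution, with misrating placed in the treated group and in its favour, 5–20% misrating by one grade would use up 13–50% of the target effect and raise the rejection rate from 5% to between about 6% and 25%. These figures show sensitivity; they do not estimate the bias in this study.

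The stronger inference that masked raters would avoid the bias is not supported. Patients and relatives know the treatment, and the mRS rests partly on what they report. Masking reduces the bias. The change is worth making but is not a fatal flaw.

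**What to change.** Amend the rule under Mandatory Training of Scales so that ratings are done by trained site staff who take no part in giving the treatment and do not know whether the patient received Cerebrolysin. Specify that the rater works without the medication chart, and add an eCRF item recording whether the rater became aware of exposure. Report the rate of unmasking by group.

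Any analysis restricted to ratings that stayed masked should be labelled supportive only. Unmasking happens after exposure and may depend on group, site and patient, so that subset can itself be biased.

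The cost is a wording change, one recorded item and a short table. Separate raters are already required, so new posts should not usually be needed, but some sites may have to name a different existing colleague. Masking will be incomplete, and the recorded item shows by how much.
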